## Abstract

**Background:**

Chronic kidney disease is an important public health threat. Such patients present high morbidity and mortality due to cardiovascular disease, with low quality of life and survival, and also high expenditure resulting from the treatment. Arterial hypertension is both a cause and a complication of kidney disease; also, arterial hypertension is a risk factor for cardiovascular disease among patients with kidney diseases. There is some evidence that exercise interventions may be beneficial to chronic kidney disease patients, but previous studies included only end-stage patients, i.e. those undergoing dialysis. This study aims to evaluate the effect of exercise on kidney function, quality of life and other risk factors for cardiovascular disease among non-diabetic chronic hypertensive kidney disease patients who are not undergoing dialysis.

**Methods:**

The participants will be located through screening hypertensive patients attended within the public healthcare network in Pelotas, a city in south of Brazil. Eligible individuals will be those with glomerular filtration rate between 15 and 59 ml/min x 1.73 m^2^. The randomization will be done in fixed-size blocks of six individuals such that 75 participants will be allocated to each group. At baseline, information on demographic, socioeconomic, behavioral, anthropometric, blood pressure and quality-of-life variables will be collected, and laboratory tests will be performed. The intervention will consist of three weekly physical exercise sessions lasting 60–75 minutes each, with a total duration of 16 weeks. The outcomes will be the kidney function progression rate, quality of life, blood pressure, lipid profile, hemoglobin level, ultrasensitive C-reactive protein level, and ankle-arm index. The patients in both groups (intervention and control) will be reassessed and compared partway through the study (8^th^ week), at the end of the intervention (16^th^ week) and in the 8^th^ week after the end of the intervention.

**Discussion:**

There is still a scarcity of data relating to the effect of physical exercise among the most numerous group of individuals with kidney disease, i.e. patients undergoing conservative treatment. In particular, there is a lack of randomized controlled studies. This study will help fill this gap.

## Background

Chronic kidney disease is an important public health threat [1]. Studies in several countries have estimated that around 12% of the population presents kidney dysfunction (glomerular filtration rate < 60 ml/min x 1.73 m^2^) and that this rate becomes greater with increasing age [2-4]. Patients with chronic kidney disease present high morbidity and mortality due to cardiovascular diseases (DCV) [5], with low quality of life and survival [6].

These patients present diminished kidney function most frequently as a result of diabetes mellitus or systemic arterial hypertension. Systemic arterial hypertension is both a cause and a complication of chronic kidney disease and hypertension is a risk factor for cardiovascular diseases among these patients [7]. Kidney disease patients who are not undergoing dialysis have been studied less often than those receiving dialysis. Strategies are required for keeping these patients’ kidneys functioning and attenuating the risk factors for cardiovascular diseases. Physical inactivity may be an important determinant of morbidity and mortality among these patients [8].

Among the general population, physical activity is associated with lower cardiovascular risk [9]. Individuals of all ages and both sexes benefit from moderate-intensity physical activity, with diminished risk of cardiovascular diseases, maintenance of muscle strength, maintenance of the ability to remain independent, reduction of the risk of falling, fewer symptoms of depression and anxiety and improved quality of life, with increased psychological and physical wellbeing [10]. Physical activity is inversely associated with rates of kidney dysfunction among diabetic patients [11,12]. Despite this evidence, patients with chronic kidney disease tend to be inactive [13]. Moreover, most experimental studies have only included in the intervention group the healthier portion of the patients indicated for kidney replacement therapy, thus making it difficult to extrapolate the results to the whole population undergoing dialysis.

Data on the effect of physical exercise among the most numerous group of individuals with chronic kidney diseases, i.e. patients at less advanced stages of the disease who are still receiving conservative treatment, are still scarce [13]. Furthermore, most studies that have dealt with this influence on chronic renal disease patients were conducted in high-income countries, involving small samples, with short intervention periods, and few were randomized and controlled. There is therefore a need for good-quality data regarding the impact of physical exercise on the prognosis for patients with chronic kidney diseases, and especially in relation to the large group of individuals with kidney diseases in its earliest stages. In addition to the cardiovascular and quality-of-life benefits from interventions, this group also presents the characteristic of potential delay in the progression of nephropathy, which is a benefit that can no longer be expected among the group indicated for kidney replacement therapy. Also, there is an urgent need to reduce the burden of cardiovascular events and the numbers of individuals with indications for dialysis among this population.

### Objectives and main measurements

The aim of the present study is to evaluate the effect of an exercise program on non-diabetic hypertensive patients with chronic kidney disease with regard to disease progression and quality of life. The hypothesis is that patients with chronic kidney disease who perform physical exercises (intervention group) will present less deterioration of kidney function and an increase in the quality-of-life score. Quality of life will be measured by means of the Medical Outcomes Study 36-Item Short Form Health Survey (SF-36), using the Portuguese version translated and validated by Ciconelli [14].

Additionally, the efficacy of the physical exercise will also be assessed by comparing the intervention and control groups regarding the following variables: (a) blood pressure and the need to use antihypertensive medications; (b) serum levels of total cholesterol, HDL cholesterol, triglycerides, albumin, ultrasensitive C-reactive protein, hemoglobin and hematocrit; (c) excretion of proteins and creatinine in urine; (d) ankle-arm index;

## Methods

### Design and setting

A randomized controlled trial will be conducted among patients with chronic kidney disease. The study will be supervised within the Postgraduate Program in Epidemiology in conjunction with the School of Physical Education of the Federal University of Pelotas, which is located in the city of Pelotas, in the south of Brazil. The sample will be composed of non-diabetic individuals presenting systemic arterial hypertension with a glomerular filtration rate of between 15 and 59 ml/min x 1.73 m^2^ (therefore characterized as being in stages 3 or 4 of chronic kidney disease [1]), who are attending primary health care units in the urban zone of the city.

### Recruitment and eligibility

The records of the “HiperDia” project, held by the City Health Department, contain the numbers of individuals with systemic arterial hypertension registered at each primary health care unit in the municipality [15]. After obtaining the names of these patients, their medical files at the primary health care units will be reviewed. Non-diabetic patients with diagnoses of systemic arterial hypertension who in 2009 presented serum creatinine levels greater than or equal to 1.0 mg/dl and glomerular filtration rates (as calculated using the Diet in Renal Disease four variables assessment formula) [16] between 15 and 59 ml/min x 1.73 m^2^ will be identified.

### Exclusion criteria

The following patients will be excluded from the study:

a) Diabetics – we opted to exclude patients with diabetes because they present different prognosis as compared to chronic kidney disease patients without diabetes [17];

b) Individuals with severe physical disabilities (stroke sequelae, lower-limb amputation without a prosthesis, and orthopedic diseases that worsen with exercise);

c) Individuals with a history of acute myocardial infarction over the last six months;

d) Individuals with kidney transplants or who are undergoing dialysis treatment.

### Sample size calculation

Due to the lack of baseline population-based Brazilian data on kidney function, we carried out a pilot study in a subsample of hypertensive patients registered in eight primary health care units in the city of Pelotas in 2010 in order to obtain the estimates needed for the sample size calculation. Through reviewing 3800 medical files, 290 patients with glomerular filtration rates of less than 60 ml/min x 1.73 m^2^ were identified. In this subsample, the glomerular filtration rate of non-diabetic hypertensive patients in stages 3 and 4 of chronic kidney disease was 48.47 ± 9.61 ml/min x 1.73 m^2^. To identify a post-intervention difference greater than or equal to 10% between the intervention and control groups that is significant at the 5% level (two-tailed), with a power of 80% at the end of 16 weeks, it will be necessary to include 63 patients in each group of the study. We decided to expand the sample to 75 patients per group in order to take follow-up losses into account based on previous trials with chronic kidney disease patients. This sample size also allows detecting baseline vs. post-intervention differences of 10% or greater in both groups.

### Random allocation

Random allocation will be performed after the individuals who agreed to participate have been interviewed and have undergone a physical examination. The allocation list will be concealed and patients will be allocated to either the intervention or the control group. In order to balance the groups in terms of numbers of participants, we will use the technique of randomization in fixed-size blocks of six individuals. For each group of six individuals, we will make a draw for the order of entry in each group (intervention or control).

The individuals identified from the “HiperDia” records will be visited at home and invited to participate in the study. After recruitment, a baseline study will be conducted to assess the individuals of both groups before the intervention. The main variables to be collected will be: demographic and socioeconomic data (sex, age, socioeconomic level, schooling level, skin color and marital status); behavioral characteristics (physical activity, smoking and alcohol consumption); anthropometric data (weight, height and waist circumference); clinical data (length of time with diagnosis of hypertension, blood pressure in the upper and lower limbs and anti-hypertensive medications currently used); venous blood and urine sample collection for laboratory analyses (hemogram, lipid profile, blood glucose, serum albumin, ultrasensitive C-reactive protein, proteinuria and creatininuria); and quality of life. The blood and urine samples will be collected at home following an overnight fast (~12 hours) by a nursing technician, and will be sent to the support laboratory, packed in refrigerated boxes at a temperature of approximately 4 °C. Interviewers will be blinded to the interventions or control status of each patient.

These patients will be interviewed again at home partway through the study (in the 8^th^ week), just after the end of the intervention (16^th^ week) and in the 8^th^ week after the end of the intervention (Figure 1). At these three visits, a short version of the baseline questionnaire will be applied, and the anthropometric and blood pressure measurements and laboratory tests will be redone. Again, interviewers will be blinded for the intervention or control status of each patient. All the laboratory tests will be performed in a single laboratory, in order to ensure comparability. The questionnaires and the physical examinations will be applied to the participants by previously trained medical students and resident physicians within clinical medical at the School of Medicine of the Catholic University of Pelotas, under supervision by the study coordinator. In all the evaluations, 10 % of the subjects will receive a telephone call from the fieldwork supervisor for quality control purposes.

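### A single fixed block size of six leaves avoidable room for certain foreknowledge of allocations if patients are allocated one by one

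*Protocol article*

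**What the plan says.** The abstract states: "The randomization will be done in fixed-size blocks of six individuals such that 75 participants will be allocated to each group". The Random allocation section gives the same block size, "we will use the technique of randomization in fixed-size blocks of six individuals", with balance in numbers as the only reason, and describes the procedure as follows: "For each group of six individuals, we will make a draw for the order of entry in each group (intervention or control". No stratification is described.

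The same section contains three safeguards:

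- On concealment: "The allocation list will be concealed".
- On timing: "Random allocation will be performed after the individuals who agreed to participate have been interviewed and have undergone a physical examination".
- On blinding: "Interviewers will be blinded to the interventions or control status of each patient". This is repeated for the follow-up visits.

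The comparison is supervised exercise against usual primary care (Intervention and procedures). Intervention patients are telephoned the day before sessions and visited at home after an absence (Follow-up and adherence to the study). A research assistant keeps the attendance record at the sessions (Quality control).

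**The concern.** In a block of exactly three and three, once one group has received its three patients the rest of the block is determined. Concealing the list does not prevent this deduction, because it is made from allocations that have already become visible. In this trial they do become visible to some people: the patients themselves, the exercise professionals, and whoever telephones, transports or records intervention patients.

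If such a person also affects who is approached next, or when, the composition of the groups could be steered, for example by bringing forward a fitter patient when an exercise place is due. Eligible patients are visited at home and invited, so the order of approach is not obviously fixed. One exclusion, for orthopaedic disease made worse by exercise, calls for judgement. The planned t-test between groups (Data colleting and analysis) would not correct selection bias of this kind.

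**Working it through.** **Inputs.** Block size 6, 1:1, 75 per group (Abstract, Methods; Random allocation). The article gives no predictability figure to reproduce. Its allocation figures do agree with each other: 2 × 75 = 150 patients, and 150 / 6 = 25 complete blocks, each with 3 + 3.

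**Assumptions for the calculation.** Patients are allocated one at a time. The observer knows the block size, where each block starts, and every earlier allocation in the block.

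**Certain predictions, fixed block of six.** There are C(6,3) = 20 equally likely orders. The number of forced places equals the length of the run of identical allocations that ends the block.

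- Exactly 1 forced: the last two differ, (2 × 3 × 3) / (6 × 5) = 0.6.
- Exactly 2 forced: the last two agree (0.4) and the third from last differs (3/4), 0.4 × 0.75 = 0.3.
- Exactly 3 forced: 0.4 × 0.25 = 0.1.

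Mean = 1 × 0.6 + 2 × 0.3 + 3 × 0.1 = 1.5. The general formula for m per arm, 2m/(m + 1), gives 6/4 = 1.5. As a share this is 1.5 / 6 = 25%, and over 25 blocks it is 37.5 of 150. The last place of each block is always forced, so at least 25 of 150 (16.7%) are known to this observer.

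**Best guessing, fixed block of six.** Always guessing the group with more places left gives m + 2^(2m−1)/C(2m,m) − 1/2 = 3 + 32/20 − 0.5 = 4.1 correct of 6, or 68.3%, against 50% with no information. Enumeration of the 20 orders gives the same 1.5 and 4.1.

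**Effect of varying the block size.** The candidate sizes are an assumption, since the article names none. The figures come from simulating 1,500 lists of 150 patients, with an observer who knows the candidate sizes and the full history and updates on them.

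| Block sizes | Known with certainty | Best guess correct |
|---|---|---|
| 6 (fixed) | 25.0% | 68.3% |
| 4, 6 | 5.5% | 69.2% |
| 6, 8 | 3.8% | 67.2% |
| 4, 6, 8 | 2.2% | 68.0% |

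With sizes 4, 6 and 8, certain predictions fall from 37.5 to about 0.022 × 150 = 3 patients. Overall guessing hardly changes.

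**Imbalance.** If recruitment stops inside a block, the groups can differ by at most half the largest block, that is 4 with a maximum size of 8. At worst this gives 77 against 73. The variance of the difference then rises by the factor (1/77 + 1/73) / (2/75) = 0.026686 / 0.026667 = 1.0007, which is negligible.

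**The case against.** The strongest reply is that the observer assumed above is not described anywhere in the article. Interviewers are stated to be blinded. Interviews and examinations are done by medical students and residents of one university, while the sessions are run by physical education professionals at another, so those who see allocations are described separately from those who assess patients. Candidates come from a registry and a file review with listed exclusions, which limits discretion. Allocation follows agreement, interview and examination, so the result of a draw cannot shape those assessments. This largely stands. What remains is foreknowledge before a patient is approached, held by someone who spans both sides. The coordinator is a possible example: this role supervises those applying the questionnaires and also monitors the study day to day. The article does not say that the coordinator learns allocations or sets the order of visits.

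Second, the sentence about making a draw for each group of six can be read as allocating six enrolled and assessed people together. On that reading sequential prediction does not arise. The mention of an order of entry points more towards one-by-one allocation, but the text does not settle it.

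Third, varying the block size does not lower overall guessability. That is correct; its benefit is confined to certain predictions.

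A reader might infer that a quarter of allocations are predictable simply because of the design, that concealment has failed, or that publishing the block size gave it to recruiters. The documents support none of these. The 25% is an expected maximum for a fully informed observer, no breach is shown, and nothing indicates that field staff were told the block size. Nor is it a defect that the article does not name the list holder, since an article commonly leaves that detail to the full protocol.

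**Conclusion.** The point holds as a minor and inexpensive improvement to a rule that the article states; it is not an error or a contradiction. With one-by-one allocation, a fixed block of six lets a person who knows the block size, the boundaries and the past allocations foresee on average up to 25% of allocations with certainty. This matters only if that person can also influence enrolment. The stated safeguards make such a person less likely without excluding one. If blocks are drawn in batches after enrolment and assessment, the concern falls away.

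One gap in the timing safeguard bears on this. Allocation is placed after the interview and physical examination, but the blood sample is not named among the steps that must come first. The primary kidney measure is estimated from serum creatinine, so the sequence is worth stating explicitly.

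**What to change.** Either of two changes to the Random allocation section is enough.

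1. Replace the fixed block of six with permuted blocks whose sizes vary at random, for example 4, 6 and 8, and keep the sizes out of documents that field staff use. The cost is a regenerated list and a final difference of at most 4 patients with these sizes.
2. Keep blocks of six, but state that each block is drawn only once six consented patients have completed all baseline measurements, including the blood sample. The cost is that the first patients in a block wait for the sixth, so the interval between baseline and the start of the intervention may lengthen.

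Under the first option, also state that each allocation is released only after all baseline measurements, including the blood sample, have been completed. This adds one sentence and no patients.

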**Figure 1 F1:**
[figure not shown]
Description of the study protocol.

### Intervention and procedures

The intervention will consist of 16 weeks of physical exercise sessions lasting for an average of 60–75 minutes, at a frequency of three sessions per week. One of the basic principles of exercise training is the progression of intensity, duration or frequency [18]. In our intervention, the progression will be based on two main variables: (a) increases in the effort-rest ratio; (b) reduction in the cool-down time of the sessions, with an increase in the main part of the classes. The workout intensity will be controlled by means of Borg’s Perceived Exertion Scale applied for Resistance Exercise [19].

All patients from the intervention group will be submitted to an acclimation period, in which light and moderate-intensity activities will be prioritized. The intervention will comprise aerobic activities, resistance training and muscle power training. The workout sessions will be composed of an initial section of 5 to 10 minutes of body warm-up and stretching exercises, a main section of circuit or interval training [19-21] with aerobic and resistance exercises lasting for 30 to 35 minutes, and 10–15 minutes of core muscles endurance and flexibility. The final part of the class will be composed of stretching and relaxation exercises lasting approximately 10 minutes.

Resistance training from weeks 1–10 will comprise multi-joint exercises (squat, curved row, bench press, upright row and biceps curl plus shoulder extension), and from weeks 11–16, we will also include low-intensity plyometric training. In terms of muscle power training, we will conduct 2–3 repetitions of 4–6 simple horizontal jumps in the first 14 weeks. In the last two weeks, vertical jumps will also be included [22].

The control group will continue to receive the usual attendance provided by the primary health care unit, in accordance with the guidelines of the Ministry of Health’s primary healthcare manuals for clinical prevention of cardiovascular, cerebrovascular and chronic kidney diseases [23]. The control group patients will answer the same questionnaires and will undergo all the physical examinations and laboratory tests at the baseline, in the 8^th^ and 16^th^ weeks after the start of the intervention and in the 8^th^ week after the end of the intervention, similarly to what will be done with patients from the intervention group.

### Follow-up and adherence to the study

Since the aim of the study is to assess the efficacy of the intervention, strategies for ensuring follow-ups with complete adherence will be used. At the start of the study, the participants will be informed about the importance of the follow-up, and the names, addresses and telephone numbers of two individuals who are close to the participant and who might be able to inform where the participant can be found will be recorded. Over the course of the study, the participants in the intervention group will be contacted by telephone on the day preceding the physical activity sessions. Participants will be offered a snack at the end of each intervention session, transportation vouchers for them to come to the sessions and a pair of training shoes and sports clothes to use at the physical exercise sessions. Participants who do not come to one of the sessions will be sought in their homes to find out why they had been absent. If necessary to ensure adherence, the study will provide door-to-door transportation, free of charge for participants. The intervention will take place between August 2011 and July 2012. The sessions will be administered by physical education professionals, through an agreement with the School of Physical Education of the Federal University of Pelotas, within the premises of the school.

